#### Concealment mechanism {16b}

Participants will be randomized using the program Study Randomizer (studyrandomizer.com), which is a web-based randomization service. Allocation concealment will be ensured, as the service will not release the randomization code until the patient has been recruited into the trial, which takes place after all baseline questionnaires and measurements have been completed.

#### Additional consent provisions for collection and use of participant data and biological specimens {26b}

Not applicable, no biological samples will be collected.

## Interventions

Explanation for the choice of comparators {6b}

Participants will be randomly assigned to one of the following two groups: (1) Control group that will only receive usual care or (2) Intervention group that will receive daily ES and usual care.

### Intervention description {11a}

#### Usual care

The control group will only receive usual care according to the national multidisciplinary guideline “Pressure ulcer prevention and treatment” (Decubitus preventie en – Behandeling) [21], i.e. the Dutch translation of the international guidelines of the National and European Pressure Ulcer Advisory Panel [22]. These guidelines consist of multidisciplinary advice on choosing an adequate wheelchair, anti-pressure ulcer cushion, (air-) matrasses, healthy lifestyle, nutrition, transfer training, learn to perform pressure-relief movements and psychosocial therapy (if needed).

#### Intervention group

The intervention group will receive usual care plus ES. ES will be applied using a 4-channel portable stimulator (EMP 4 Eco+; Wuxi Jiajian Medical Instrument Co., Ltd; China) connected with surface electrodes, either self-adhesive electrodes or a custom-made lycra garment with built-in surface electrodes (Berkelbike BV, Sint-Michielsgestel, NL). The researchers decide who receives a garment or surface electrodes while looking at the following criteria; the participant’s choice, functionality, independence, the presence of wounds on the back and the presence of a stoma. ES will be given for at least 60 min bi-phasically with a 6 s:18 s activation-rest cycle, 50 Hz (frequency), a 300–400-μs pulse duration and the output current amplitude (mA) will be determined per participant. The current amplitude resulting in the best tetanic contraction without creating discomfort or excessive muscle contractions will be determined for each participant individually during the baseline measurement by the ES expert or research assistant. This amplitude will be used as starting point for the home stimulation, participants will be instructed to increase the mA if no activation or only twitches are visible. The activation within the activation-rest cycle consists of 2 s ramp-up, 3 s full activation and 1 s ramp-down followed by 18 s rest. The 6 s:18 s activation-rest cycle is based on the 1:6 cycle which has been proven to be effective and seems more effective than a cycle with less rest [34, 37]. The 1:6 cycle is multiplied by 3 to create a longer contraction and rest period, which might lead to a lower risk for long-term muscle fatigue. The researchers present it as a 6 s:18 s activation-rest cycle, since the ramp-up and down are also seen as activation.

### Criteria for discontinuing or modifying allocated interventions {11b}

When one of the following adverse events or inconveniences occurs during ES, the intervention needs to be stopped temporarily:
Red, raised or itchy skin [38–40]Muscle pain [38, 40]Increase in nerve painFeeling uncomfortable [38, 40]Orthostatic hypotension: dizziness, light-headedness, blurred vision, palpitation or shortness of breath [38, 41]Autonomic dysreflexia, dysfunction or dysregulationPain induced by spasms

The adverse events mentioned above are temporary and usually disappear once the stimulation has stopped. If problems continue to arise during stimulation, the intervention will be stopped.

### Strategies to improve adherence to interventions {11c}

Not applicable, this trial will not use strategies to improve adherence to the intervention.

### Relevant concomitant care permitted or prohibited during the trial {11d}

Not applicable, this trial does not have concomitant care permitted or prohibited.

#### Use of co-intervention

During the intervention period, participants will be asked not to participate in any other ES-induced exercise program, or to participate in any other study that may interfere with the current study.

### Provisions for post-trial care {30}

The materials provided to the intervention group such as the adhesive surface electrodes of the ES garments may be kept for personal use. The stimulator EMP4 ECO+ needs to be handed in at the last physical measurement. If the intervention shows to have a positive effect, the control group will receive advice and guidance about ES after the study is completed.

### Outcomes {12}

PU incidence, the primary outcome parameter, will be monitored every 2 weeks throughout the 12-month study period. Secondary outcome parameters (i.e. potential PU risk factors, mobility limitations, health-related quality of life, participation and usability of the ES system) will be evaluated at baseline (T0) and after 3 (T1), 6 (T2) and 12 months (T4). Cost data will be gathered at baseline and every 3 months so also at 9 months (T3). Process evaluation questionnaires will be administrated every 3 months and interviews will be performed at 3 and 12 months. Table 1 provides an overview of all assessment moments and when the measurements take place.

**Table 1 Tab1:** Schedule of assessments and overall measurements

Time (months)	0	1	2	3	4	5	6	7	8	9	10	11	12
**Time points**	**T0**			**T1**			**T2**						**T3**
**Primary outcomes**													
New PU*		X	X	X	X	X	X	X	X	X	X	X	X
Picture		X	X	X	X	X	X	X	X	X	X	X	X
**Secondary outcomes*****: PU risk factors***													
Blood flow	X			X			X						X
Muscle thickness	X			X			X						X
Interface pressure distribution	X			X			X						X
**Secondary outcomes*****: Questionnaires***													
PASPID	X			X			X						X
WHO-QoL-5	X			X			X						X
USER-participation	X			X			X						X
SIP-68	X			X			X						X
HADS	X			X			X						X
PSQI	X			X			X						X
FSS	X			X			X						X
Self-care capacity	X			X			X						X
***Usability and user-friendliness of the ES system***													
Self-administrated questionnaire				X			X			X			X
Diary		X	X	X	X	X	X	X	X	X	X	X	X
***Cost analysis***													
EQ-5D-5L	X			X			X			X			X
Online cost questionnaire	X			X			X			X			X
***Process evaluation***													
Questions of the RE-AIM model				X									X
Interviews				X									X
Focus group													X

*Every 2 weeks (if the answer is yes, also data are collected about the number of days bedrest AND absence of work)

#### Baseline characteristics

At baseline, the following determinants, which can have an effect on developing PUs and are potential confounders, are also collected: age, sex, cause of SCI, level of SCI, Asia Impairment Scale, time since injury, rehabilitation centre, number of PUs in the past, locations of PUs in the past, PU surgery in the past (yes/no and how often), type of surgery, comorbidities (heart and vascular, stomach liver, intestinal or kidney disease, bladder, urinary or respiratory problems, diabetes, history with cancer, musculoskeletal or other neurological disorders) and spasms (yes/no and if yes, which muscles).

#### Primary outcome

##### Pressure ulcer incidence

PU incidence in the sacral or ischial tuberosity’s region (in total and for each severity category according to the EPUAP [22]) will be recorded throughout the 12-month study period by the participant or his/her caregiver. Every 2 weeks, each participant will receive an email or notification with the question of whether a new PU has been identified or whether an existing PU is still present. If the answer is ‘yes’ then the following steps need to be taken:
A digital photo of the wound will be made by the participant or his/her caregiver according to standardized instructions and will be sent to a nurse practitioner specialized in wound care. All pictures will be analysed by the same well-trained and experienced nurse practitioner. The location of the wound and the severity (category 1–4) will be classified according to the EPUAP [22]. If there is a wound visible in the photo the wound is also evaluated with the TIME model, a method for evaluating local disruptive factors [21].Change in risk score will be evaluated with a modified CBO list, derived from the main elements of the Norton, Waterlow, Braden scale and 2 Dutch lists, i.e. PrePURSE and CBO list [1].(Possible) Cause of PU needs to be described by the participant.Healing tendency will be calculated by the experienced nurse practitioner by dividing the starting content (depth wound) or surface (superficial wound) by the number of days to complete wound healing. The outcome will be the average number of surface area reduction per day. This can only be done in case of a wound severity category 3 or 4 [42].

Each participant will be asked to take a standard photo of the sacral and ischial tuberosities regions every month. This picture should be taken regardless of a pressure ulcer is present.

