**Methods:**

A multicentre randomized controlled trial (SCI PREVOLT) will be conducted with an economic and process evaluation alongside. One hundred participants with a SCI in the chronic phase and a minimal incidence of 1 PU in the last 5 years will be recruited from rehabilitation centres across the Netherlands. Participants will be stratified by centre and age and randomized to the intervention or control group. The intervention group will use ES at least 1 h/day during at least 4 times a week for 1 year next to usual care. The control group will only receive usual care. The primary outcome is the incidence of PUs, measured by a blinded person assessing the presence or absence of a PU on the buttocks on a photo made by the participant or his/her caregiver. The incidence of a PU will be evaluated every 2 weeks. Secondary outcomes include interface pressure distribution, blood flow in the profunda femoris artery, muscle thickness of the hamstrings and gluteal muscles and questionnaires about different dimensions of life, e.g. participation and quality of life. Secondary outcomes will be measured at baseline and 3, 6, 9 and 12 months after randomization.

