### Plans to promote participant retention and complete follow-up {18b}

Every 2 weeks, participants will get an invitation to fill in some questions regarding the PU incidence and the intervention group will also be asked to complete the diary. When opening the online questionnaire, an overview is visible showing which questionnaire has already been completed and which questionnaire has not yet been completed. When a questionnaire is not fully completed or submitted a week after the invitation, the local researcher of Reade will contact the participant.

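### The wound photo follows a 'yes' at the two-weekly prompt rather than first notice, and the plan does not settle whether a reported ulcer with no visible wound counts as a primary event

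*Protocol article*

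**What the plan says.** All references are to the protocol article.

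- **Abstract, Methods.** The primary outcome is PU incidence, "measured by a blinded person assessing the presence or absence of a PU on the buttocks on a photo made by the participant" or by a caregiver. Section {17a} agrees: it names the wound nurse's reading of the digital photos as the primary outcome and says that the nurse is blinded throughout.
- **Pressure ulcer incidence.** Here incidence is recorded by the participant or caregiver. The prompt is two-weekly: "Every 2 weeks, each participant will receive an email or notification with the question of whether a new PU has been identified", or an existing one persists. Then: "If the answer is ‘yes’ then the following steps need to be taken". The first step is "A digital photo of the wound will be made by the participant or his/her caregiver according to standardized instructions", sent to the nurse for location and category 1–4.
- **Same section, photo without a wound.** "If there is a wound visible in the photo the wound is also evaluated with the TIME model". The plan thus foresees a photo that shows no wound, but does not say how that report is scored.
- **Same section, monthly photo.** A standard photo of the region is also due every month whether or not an ulcer is present. Table 1 lists it under primary outcomes.
- **Section {18b}.** "When a questionnaire is not fully completed or submitted a week after the invitation", the researcher contacts the participant.
- **Effect analysis.** The dependent variable is whether the participant had any PU over 12 months, yes or no.

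**The concern.** Nothing in the article asks for a photo when an ulcer is first noticed. If the steps are followed as written, an ulcer that opens and closes between two prompts gets a truthful 'yes', because the question asks what has been identified, but the photo taken afterwards may show healed skin. Category 1 is in scope, so mild, short-lived lesions are the most exposed.

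What then happens depends on which section is followed. If the photo decides, those ulcers drop out. Events are lost, power falls, and the endpoint becomes partly a measure of how long an ulcer lasts. If the participant's 'yes' decides, the endpoint rests on self-report by people who know whether they use ES, and blinding the photo reader no longer protects it. Either way, the trial's only primary endpoint carries an ambiguity that could be removed cheaply.

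**Working it through.** **The plan's own figure.** The sample size section gives 45 per group for 35% vs 10%, alpha 0.05 and 90% power, and 50 per group after 10% dropout (45/0.9 = 50). The usual formulas give 44 to 46 per group with a one-sided alpha of 0.05, and 57 (pooled) with a two-sided one. Sidedness is a separate matter. It is mentioned only because it fixes the baseline used here: two-sided power at 45 per group is 82% by the normal approximation and 85% by exact binomial enumeration of the uncorrected chi-square test. The exact figure is used below.

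**Assumptions, none from the document.** Onset is uniform within a 14-day interval, duration is exponential with mean m days, each affected person has one ulcer, the photo decides, 35% and 10% are incidences before any photo loss, and the monthly photo gets no credit.

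**Share still visible at the next prompt:** c(m) = (m/14) × (1 − exp(−14/m)). For m = 14: 1 × (1 − e⁻¹) = 0.632.

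**Power** is then computed for 35% × c vs 10% × c at 45 per group.

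| Mean duration | Visible, c | Observed rates | Exact power |
|---|---|---|---|
| no loss | 100% | 35.0% vs 10.0% | 85% |
| 14 days | 63% | 22.1% vs 6.3% | 61% |
| 28 days | 79% | 27.5% vs 7.9% | 73% |
| 42 days | 85% | 29.8% vs 8.5% | 77% |

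For a mean of 7 days, c is 43%. A late responder who also delays the photo by 7 days multiplies c by exp(−7/m); for m = 14 this is 0.632 × 0.607 = 38%.

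**Credit for the monthly photo.** Its timing is not fixed. If it coincides with a prompt, it adds nothing. If it falls midway in every second interval, the share becomes ½ × (m/14)(1 − exp(−14/m)) + ½ × (m/7)(1 − exp(−7/m)): 53% (m = 7), 71% (14) and 84% (28). Exact power is then 67% for m = 14 and 76% for m = 28.

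**More than one ulcer per affected person.** With two independent ulcers, the chance that at least one is seen is 1 − (1 − c)². For m = 14 this is 1 − 0.368² = 86%, with power about 77.5%; for m = 28, 95% and about 82%.

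**If ES shortened healing but prevented nothing** (35% in both arms):

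| Mean duration, control vs ES | Apparent rates | Difference | Risk ratio | Chance of a significant result favouring ES |
|---|---|---|---|---|
| 14 vs 7 days | 22.1% vs 15.1% | 7.0 points | 0.68 | 14% |
| 28 vs 14 days | 27.5% vs 22.1% | 5.4 points | 0.80 | 9% |
| 21 vs 14 days | 25.5% vs 22.1% | 3.4 points | 0.87 | 6% |
| 42 vs 28 days | 29.8% vs 27.5% | 2.2 points | 0.93 | 4.5% |

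With no difference at all (35% in both arms, full capture), that chance is 2.6%.

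**The case against.** **The unseen instructions.** The photo is to follow standardized instructions that are not shown, and an article condenses its full protocol. Those instructions may already ask for a photo at first notice, and nothing in the article forbids sending one taken earlier. This stands as a limit on certainty. It does not remove the point, because the article states a sequence (prompt, 'yes', photo) and gives two accounts of what determines the outcome.

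**'Healed ulcers are scored as absent.'** A reader might infer this, but it is written nowhere. It follows from the abstract and section {17a}, whereas the outcome section speaks of incidence recorded by the participant and of a question that looks back over the interval. What the text supports is that the case is undefined.

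**'The photo is taken only after a yes.'** This too goes beyond the text, since the monthly photo is unconditional. It can only shorten gaps, but it is not tied to onset and leaves a good part of the loss in place.

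**'Faster healing will be counted as prevention.'** The document does not claim that ES speeds healing of an existing ulcer; its rationale concerns pressure, muscle mass and circulation. The background also describes prolonged bed rest as very often part of treatment, which suggests that many ulcers last long enough to be seen.

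**The power figures.** They sit towards the pessimistic end. Repeat ulcers soften them, as shown above. If the planned 35% already refers to detected ulcers, part of the loss is counted twice.

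**Conclusion.** The point holds as a weakness in how the primary outcome is captured and defined, not as a demonstrated bias. Two statements are supported. The wound photo is tied to the prompt rather than to first notice, and the sections do not agree on whether a reported ulcer with no visible wound is an event.

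The size cannot be known from the document. Under assumed mean durations of 14 to 42 days, one ulcer per person and no credit for the monthly photo, 63% to 85% of ulcers would be visible and two-sided power would fall from about 85% to 61% to 77%. Long-lasting ulcers would mostly be caught. The power loss needs no assumption about healing under ES.

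A spurious benefit would need ES to shorten healing as well. For the scenarios tried it is about 2 to 7 points, well below the planned 25. It should be presented as a possibility, not as an expected result. The change is worth making because it is cheap and concerns the primary endpoint.

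**What to change.** 1. In both arms, instruct participants and caregivers to photograph any suspected ulcer on the day it is first noticed and to submit the dated photo then or with the next two-weekly form. The blinded nurse reads that photo.
2. State in the outcome section that the blinded photo reading decides the primary endpoint, so that it agrees with the abstract and section {17a}.
3. Record a 'yes' without a photo from when the ulcer was present as 'reported, not verifiable', and count these reports as events in a sensitivity analysis.
4. If the standardized photo instructions already require a photo at first notice, bring the outcome section into line with them.

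The cost is one line in the instructions and one field in the two-weekly form. The sample size is unchanged. The downside is some unscheduled uploads and a few more photos for the same nurse. The healing measure for categories 3 and 4 would also gain, because its starting size would be taken closer to onset.

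### The healing-tendency formula puts volume and area rates under one area label and gives no value to ulcers still open at 12 months (minor; primary analysis unaffected)

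*Protocol article*

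**What the plan says.** All the wording is in the Protocol article, Primary outcome, Pressure ulcer incidence. PU incidence "will be recorded throughout the 12-month study period by the participant or his/her caregiver". Every two weeks the participant is asked about new PUs and about whether a known PU persists. A 'yes' triggers several steps:

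- **Photo.** "A digital photo of the wound will be made by the participant or his/her caregiver according to standardized instructions". A wound-care nurse practitioner classifies location and category from it.
- **Risk score.** "Change in risk score will be evaluated with a modified CBO list".
- **Healing tendency.** The nurse practitioner calculates it by "dividing the starting content (depth wound) or surface (superficial wound) by the number of days to complete wound healing". The article continues: "The outcome will be the average number of surface area reduction per day". It then restricts the calculation: "This can only be done in case of a wound severity category 3 or 4".

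The Baseline characteristics section opens its list with "At baseline, the following determinants, which can have an effect on developing PUs and are potential confounders, are also collected". The list contains no CBO or other PU risk score. Table 1 has no row for the CBO list or for healing tendency at any time point. The Effect analysis section uses PU during follow-up, yes or no, as the dependent variable.

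**The concern.** Two features of the formula cause trouble when it is followed literally.

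1. The numerator is a volume for one kind of wound and an area for another, but the result carries one label. An average over both kinds has no unit, and a reader of the results could not tell which quantity a given value represents.
2. The denominator exists only if the ulcer closes during follow-up. Whether an ulcer gets a value therefore depends on how fast it heals and how early it starts. That is selection on the outcome itself, and it makes reported healing look faster than it was.

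A smaller, separate matter is the wording 'change' for the CBO score. As described, the list is completed only after a 'yes', so the article shows no starting value for a first PU.

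At stake is the credibility of a descriptive healing result based on few wounds. The trial's main conclusion does not depend on it.

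**Working it through.** The article states no numerical value for healing tendency, so there is no figure to reproduce. The check is of units, of when the formula is defined, and of how it behaves.

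**Units.** Content ÷ days is a volume per day; surface ÷ days is an area per day. Take an assumed wound of 10 cm² and 2 cm depth that heals in 100 days:
- content: 10 × 2 = 20 cm³; 20/100 = 0.20 cm³/day
- surface: 10/100 = 0.10 cm²/day

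Only the second fits the stated label. The described data source is a photograph, and the article describes no step that measures depth or volume.

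**Ulcers without a value.** Assume onset uniform over 365 days and a fixed healing time T. An ulcer is unhealed at the end if it starts in the last T days, so the share without a value is T/365:

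| Assumed T (days) | T/365 | Share without a value |
|---|---|---|
| 30 | 30/365 | 8% |
| 90 | 90/365 | 25% |
| 180 | 180/365 | 49% |

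With one fixed T, only late onset causes the loss. When healing times differ, slow healers are lost more often. As an illustration, let half of the ulcers take 30 days and half 180:
- with a value: 335/365 of the fast ones and 185/365 of the slow ones
- mean healing time of all ulcers: (30 + 180)/2 = 105 days
- mean among those with a value: (335 × 30 + 185 × 180)/(335 + 185) = 43,350/520 ≈ 83 days

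The bias is towards faster healing. Its amount depends wholly on the assumed healing times.

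**Dependence on starting size.** For a superficial ulcer that closes, starting area ÷ days is exactly the mean absolute area reduction per day. It depends on size in the following way:
- equal healing time of 56 days: 2/56 = 0.036 and 8/56 = 0.143 cm²/day
- circular wound with edge advance v: T = r/v, so the index is πr²/(r/v) = πrv. With v = 0.1 mm/day and r = 5, 10 and 20 mm it is 1.57, 3.14 and 6.28 mm²/day
- 1 cm² closed in 30 days gives 1/30 = 0.033; 10 cm² closed in 150 days gives 10/150 = 0.067 cm²/day
- if healing time is proportional to area, the index is the same for every size

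**How many ulcers are involved.** From the Sample size section, 35% and 10% of 50 per group are 17.5 and 5, about 22 participants with any PU. Those with category 3 or 4 are at most that many.

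**The case against.** The strongest reply is that little depends on this. Healing tendency is not among the objectives, the secondary outcomes, the rows of Table 1 or the planned analyses. It is a per-wound descriptor, no comparison of healing between groups is planned, and handling of unhealed wounds could be left to an analysis plan. The lack of a planned comparison stands and limits the severity. The analysis-plan argument stands only in part: a plan can add a rule for unhealed ulcers, but the formula as fixed excludes them, and the unit conflict can be removed only by changing the stated definition.

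Several stronger readings are tempting, and the article does not support them:

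- **That the index is invalid altogether.** It is not. For a healed superficial ulcer it is a legitimate absolute rate.
- **That smaller ulcers always score as slower healing, so that stimulation would be penalised.** This depends on how healing time scales with area, and size dependence is a property of any absolute rate. The trial's hypothesis concerns fewer PUs; the article does not say that stimulation makes them smaller.
- **That naming superficial wounds contradicts the restriction to categories 3 and 4.** The article does not define the two wound types, so no contradiction is shown.
- **That photos can yield no usable size.** The standardised photo instructions and the cited method are not reproduced, so a scale may already be required.
- **That change in risk score cannot be computed.** Table 1 omits the CBO list even where the text uses it, so its silence at T0 proves little. The baseline list is of items also collected and does not claim to be complete, and the full protocol may include the list. Change between successive 'yes' reports is possible in any case.

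**Conclusion.** The point holds in limited form, and its severity is minor. Two defects are in the text itself: a volume rate and an area rate share one area label, with no depth or volume measurement described, and an ulcer not healed within 12 months has no value. The second makes healing look faster than it is. The shares of about 8%, 25% and 49% rest on assumed fixed healing times of 30, 90 and 180 days and on uniform onset; they show direction and possible scale, not an estimate for this trial. The missing baseline for the CBO score is a point to confirm, not an established error. A reader might infer that the primary result is affected. It is not, because the effect analysis uses only whether a PU occurred.

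**What to change.** 1. For all category 3 and 4 ulcers, report time from the first report of the PU to the first fortnightly answer that it is no longer present, censored at end of follow-up or withdrawal. Every such ulcer then contributes.
2. If a rate is kept, use area only, in one unit, from the photos already requested while a PU persists. State that it describes healed ulcers only, and drop content.
3. For the modified CBO list, either confirm that it is collected at T0 or call it 'risk score at PU report' instead of 'change'.

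The cost is mainly wording, since the fortnightly answers and photos are already part of the plan. There are two drawbacks: healing dates would be known only to about two weeks, and area does not capture depth.
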